### Data management and quality control

Data will be entered into an encrypted and password-protected Microsoft® Excel database (Microsoft Corp., Redmond, WA, USA) by qualified research personnel. Appropriate range and missing data filters will be used to address data quality. Data accuracy will be assessed by random selection of 10% of individuals who will have their data confirmed by a second reviewer. Following the acquisition of the EEG data, the research staff will ensure that data is de-identified. Continuous EEG data will be de-identified by using only the participant study IDs and the date and time of measurement. All EEG data headers will be stripped of potentially identifying information to further protect participants. The confidentiality of the data collected and the identity of the individuals participating in this study will be strictly maintained. All files pertaining to subjects in the study will be coded numerically.

### Ethics statement

This study was approved by the Unity Health Toronto Research Ethics Board (protocol number 22–084). Written informed consent will be obtained from participants prior to data collection. Recruitment began on December 6, 2022 and is currently ongoing.

## Discussion

While ketamine has demonstrated considerable efficacy in the treatment of depression, some patients do not respond and it is not currently possible to predict who will benefit from this treatment [49]. Moreover, the exact mechanisms by which ketamine exerts antidepressant effects are not fully understood [50]. Based on predictive coding theories of neurocomputation [25, 33, 51], we hypothesize that ketamine’s antidepressant effects are driven by a reduction in precision due to NMDAR-antagonism and that, in turn, this potentiates learning rates and long-term plasticity expressed as increases in the conductance and effective connectivity parameters of our model.

Beyond uncovering the mechanisms of ketamine’s action, the computational parameters derived from fitting our models to patient behavior and EEG recordings may hold predictive value for individual treatment outcomes. If validated, this approach could offer valuable prognostic insights, helping to tailor treatment plans based on specific neurophysiological markers. Our modeling framework acknowledges the complex and multifaceted nature of TRD, encompassing its physiological, psychological, and social dimensions. By integrating these factors within our analysis approach, we can explore how they interact and contribute to the overall treatment response.

One limitation of this study is the lack of follow-up EEG recordings. As the last EEG recording takes place immediately before the final ketamine infusion, we will not be able to assess the effects of the final ketamine infusion on EEG measures. Additionally, we will not be able to include the long-term effects of ketamine treatment on biomedical signals in our model as we will not collect those signals at follow-up. Future studies should consider repeated follow-ups post-treatment, as this would allow for an understanding of the long-term effects of ketamine in responders and non-responders as well as the changes that underlie remission following an extended period without ketamine infusions.

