**Methods:**

This is a prospective study of 30 patients with TRD who are undergoing intravenous ketamine therapy. Prior to 3 out of 4 ketamine infusions, EEG will be recorded while patients complete the auditory MMN task. Depression, suicidality, and anxiety will be assessed throughout the study and a week after the last ketamine infusion. To translate the effects of ketamine on the MMN to computational mechanisms, we will model changes in the auditory MMN using the hierarchical Gaussian filter, a hierarchical Bayesian model. Furthermore, we will employ a conductance-based neural mass model of the electrophysiological data to link these computational mechanisms to their neural causes.

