While ketamine represents a potential breakthrough treatment for TRD, numerous aspects of its therapeutic effects are yet to be understood. While ketamine quickly alleviates depressive symptoms, these effects often require repeated infusions to be sustained [9, 12]. Furthermore, some patients with TRD do not improve despite receiving multiple infusions and it is currently not possible to predict who may benefit from this intervention in advance [13]. While changes in NMDAR-related plasticity are thought to contribute to the treatment response, the underlying neural mechanisms behind response compared to relapse are not yet elucidated [14]. Of note, the antidepressant effects of ketamine may be attributed to mechanisms other than NMDAR antagonism; multiple studies have demonstrated the roles of other receptors, such as the α-amino-3-hydroxy-5-methyl-4-isoxazolepropionic acid receptor (AMPAR), in producing antidepressant effects following ketamine treatment [15].

To address the above-mentioned challenges, we aim to elucidate the neural mechanisms of ketamine treatment by modeling ketamine-induced changes in auditory evoked potentials using the auditory mismatch negativity (MMN) paradigm. The MMN is a biological index of implicit learning, occurring when a sensory stimulus violates a statistical regularity in the environment [16]; for example, when a sequence of low tones is unexpectedly interrupted by a high tone. Formally, the MMN is defined as the difference waveform obtained when subtracting the electrophysiological response to a predictable (i.e., standard) stimulus from the response to an unpredictable (i.e., deviant) stimulus. It has long served as a marker of cognitive and functional decline in psychiatric disorders, whereby a smaller MMN amplitude corresponds with poorer levels of cognitive and psychosocial functioning [17]. Furthermore, since the MMN specifically reflects the flow of current through ion channels mediated by the NMDAR and is a relatively specific measure of postsynaptic potentials produced by the binding of glutamate to the NMDAR, it could potentially serve as a biomarker for determining whether a new treatment affects NMDAR responsiveness or to predict whether a specific patient might respond favorably to such a treatment [18].

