### Objectives

The objective of this study is to understand the computational mechanisms underlying changes in MMN following acute and repeated ketamine intervention. Subsequently, we aim to link the computational mechanisms to their underlying neural causes and use the neurocomputational model parameters to make individual treatment predictions.

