## Methods

### Participants

This will be a single-centre study of 30 participants at St. Michael’s Hospital, Unity Health Toronto, where standard of care ketamine infusions are regularly performed in a monitored setting. Patients who are scheduled to receive ketamine treatment and are interested in participating in this study will be referred to the study coordinator. Approximately six patients are scheduled to receive IV ketamine every month. Participants aged 18 to 65 years who meet the Diagnostic and Statistical Manual for Mental Disorders (DSM-5) criteria for MDD are eligible for inclusion in the study. Participants must be in a major depressive episode at the time of screening, and have a total score of ≥10 on the Montgomery-Åsberg Depression Rating Scale (MADRS) [34]. Only those who are English-speaking and competent to consent, based on their ability to provide a spontaneous narrative description of the key elements of the study, will be included. Participants must have experienced a failure of at least two trials of antidepressant therapy during the current episode (i.e., TRD) and be receiving ketamine treatment clinically as administered by their clinician. Included participants will confirm that they are on stable doses of any concomitant psychotropic medications. If any changes to concomitant psychotropic medications are required per the patient’s standard of care, the participant will be withdrawn from the study. Patients with a history of bipolar disorder, psychosis, current diagnosis of substance use disorder or history of substance use disorder during the past year, excluding nicotine and caffeine use disorder, will be excluded from participating in this study.

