### Trial design

This will be an observational study with a prospective design (Fig 1). According to the standard of care, patients will receive ketamine infusions twice a week for 2 weeks (4 total). Immediately prior to the first, second, and fourth infusions, patients will undergo an EEG scan with an auditory MMN task and simultaneous ECG recording. Clinical assessments of depression and anxiety symptoms as well as suicidal thoughts and behaviors will take place at baseline, after each ketamine infusion, and at follow-up, approximately one week after the last infusion.

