### Data analysis

#### Clinical outcomes

Response will be defined as a reduction of 50% or more in the total scores of both the MADRS and GAD-7, and a 50% or greater reduction in item 10 of the MADRS scale, from baseline to the follow-up. Remission will be defined as a MADRS total score of 10 or below, assessed at the follow-up visit. C-SSRS and GAD-7 scores will be utilized to examine the association between biomedical signals and suicide and anxiety, respectively.

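### With ketamine given to every participant and no comparator, the model parameters can forecast outcome on ketamine but cannot identify subgroups by ketamine's efficacy; the hypothesis, the Fig 3 caption and the remark on tailoring treatment should be reworded to match.

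*Protocol article*

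**What the plan says.** **Design.** The Trial design section states: "This will be an observational study with a prospective design". The abstract's Methods paragraph describes one cohort: "This is a prospective study of 30 patients with TRD who are undergoing intravenous ketamine therapy". Under Participants, eligible patients must "be receiving ketamine treatment clinically as administered by their clinician". No placebo, untreated or otherwise treated group is described.

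**Outcome.** Under Data analysis, Clinical outcomes: "Response will be defined as a reduction of 50% or more in the total scores of both the MADRS and GAD-7". The definition adds a reduction of at least half in MADRS item 10, and all changes run from baseline to the follow-up visit. Response is thus measured against the patient's own baseline.

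**Prediction claims.**
- The Introduction describes the state of the field: "it is currently not possible to predict who may benefit from this intervention in advance". Its next paragraph offers the study as a way of addressing such challenges.
- The last paragraph before Objectives hypothesises, without a conditional, that precision, AMPAR and NMDAR parameters will mark out subgroups differing in therapeutic efficacy.
- The Objectives aim to "use the neurocomputational model parameters to make individual treatment predictions".
- The Fig 3 caption presents the neural mass model as predicting ketamine's antidepressant effects in TRD.
- The Discussion says that the approach, subject to validation, could give prognostic insight, "helping to tailor treatment plans based on specific neurophysiological markers".

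**Limitations.** The limitations paragraph in the Discussion covers the absence of EEG at follow-up and its consequences. It does not mention the absence of a comparator.

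**The concern.** Benefit from a drug is the outcome with it minus the outcome without it. This study observes only the first term. A parameter that tracks natural course, regression to the mean or expectancy would look the same here as a parameter that tracks a ketamine-specific effect.

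A hypothesis about subgroups defined by efficacy is a statement about effect modification, and a single treated cohort cannot test it. If an association between parameter and outcome were reported under that hypothesis, a forecast could be read as a guide to choosing treatment. A patient with an unfavourable forecast on ketamine may still do better with it than without it, and nothing in these data would show whether that is so.

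**Working it through.** **The plan's own figures.** The document gives no figure for the size of this problem. The Sample size section expects at least 60% of patients to respond within 24 hours on ketamine and gives no response rate without ketamine. N = 30, with Cohen's f = 0.4 and 15% dropout, concerns precision. The point here is identifiability, and it would stand at any sample size.

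**What is and is not observed.** For marker group m,

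benefit(m) = P(response with ketamine, m) − P(response without ketamine, m).

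The cohort estimates the first term for each m. It carries no information on the second.

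**Illustration.** All rates here are assumptions, not taken from the document. Let the marker split patients 50/50, with response on ketamine of 80% in marker-positive and 40% in marker-negative patients. Overall response is 0.5 × 80% + 0.5 × 40% = 60%. This is chosen to match the article's expected rate, although that rate refers to 24 hours and the study's response definition to follow-up. Three possible sets of unseen rates without ketamine give:

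| Unseen rates without ketamine (marker +/−) | Benefit, marker + | Benefit, marker − | Reading |
|---|---|---|---|
| 50% / 10% | 80 − 50 = 30 points | 40 − 10 = 30 points | prognostic only |
| 20% / 20% | 80 − 20 = 60 points | 40 − 20 = 20 points | marker + gains more |
| 70% / 10% | 80 − 70 = 10 points | 40 − 10 = 30 points | marker − gains more |

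The study would see the same 80% against 40% in every row. The order of benefit between the groups can be equal, favourable or reversed. The specific rates do not matter; any on-ketamine contrast is compatible with several patterns of benefit.

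**What a test of efficacy subgroups would involve.** Assume a 1:1 comparator, a marker split 50/50, a marker-by-treatment interaction of 0.8 SD (the two-group equivalent of f = 0.4), two-sided alpha 0.05 and 80% power. With interaction variance 16·SD²/N, N = 16 × (1.960 + 0.842)² / 0.8² ≈ 197 evaluable, and 197 / 0.85 ≈ 232 with 15% dropout. With about 25 evaluable patients (30 × 0.85 = 25.5) divided over two arms, the standard error would be √(16/25) = 0.8 SD and the power about Φ(0.8/0.8 − 1.96) = Φ(−0.96) ≈ 17%. Such a test is a different study from this one.

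**Wording set against design.** The Objectives can be read as prediction of an individual's outcome under treatment, which the design supports; the sentence only needs to say so. The subgroup hypothesis and the Fig 3 caption refer to efficacy and drug effects, which the design does not identify. The Discussion sentence begins with prognosis, which is supported, and ends with tailoring of treatment, which does not follow from prognosis alone.

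**The case against.** The strongest reply is that the article does not claim what a critic might read into it. A reader who takes only the words on tailoring might infer that the study is presented as showing who benefits from ketamine or as supplying a tool for choosing treatment. The document does not support that reading. The full sentence depends on validation, says what the approach could offer, and calls the insight prognostic. The abstract Conclusion does the same. The statements about not knowing who benefits, in the abstract Background, the Introduction and the opening of the Discussion, describe a gap in the field, and that wording appears in neither the Objectives nor the abstract Conclusion. No part of the plan uses a marker to allocate or withhold treatment. The limitations are not presented as a complete list, and the single-cohort design is stated openly. Therapeutic efficacy may also be meant loosely, as degree of improvement.

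Most of this stands, and it reduces the point to a minor one. What it does not answer is that the Introduction offers the study as addressing the gap, that the subgroup hypothesis and the Fig 3 caption carry no qualification, and that validation in a further all-ketamine cohort would confirm a forecast without turning it into a basis for tailoring. If efficacy is meant loosely, saying so costs nothing.

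It would also be wrong to infer that the single-cohort design is itself a fault. It suits a mechanistic study within standard of care, and nothing here calls for a control arm.

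**Conclusion.** The point holds in a limited form. Because every participant receives ketamine and response is change from the patient's own baseline, an association between model parameters and response can support a forecast of outcome on ketamine only. The hypothesis of efficacy-defined subgroups cannot be tested as worded, the Fig 3 caption shares the problem, and the step from prognosis to tailoring needs a qualification.

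This conclusion rests on the stated design and on no numerical assumption. The response rates and the interaction sample size above are illustrative, and the document allows no estimate of how much of any observed association would be non-specific. Severity is minor: it affects what the study may conclude, not how it is run or analysed.

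**What to change.** - **Introduction (subgroup hypothesis), Objectives and Fig 3 caption:** state the target as prediction of symptom outcome, that is, the MADRS/GAD-7 response at follow-up as defined under Clinical outcomes, in patients given ketamine.
- **Discussion (tailoring sentence):** add that use of the markers to choose treatment would need data with a comparator and a marker-by-treatment test.
- **Limitations paragraph:** add that there is no comparator, so prognosis cannot be separated from ketamine-specific benefit.

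The background statements about the gap in the field can stay, and the abstract Conclusion already uses suitable wording. The cost is editorial: no data, visits or analyses change. The downside is a narrower and less attractive claim. Recruitment was still under way when the article was written, so the target could be restated before results are reported.
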